To prevent overfitting, the nonlinear modeling effects of all models will be validated via cross-validation. A 3×10-fold cross-validation scheme will be adopted, with each split performed independently, yielding 30 model performance estimates (eg, area under the curve [AUC], *F*_1_-score). Overfitting will be monitored by ensuring that the performance difference between the training set and the cross-validation set remains below a threshold (AUC difference <0.05). During cross-validation, hyperparameters (including max_depth for RF, and C and γ for SVM) will be jointly optimized to select the parameter combination that achieves the best trade-off between fitting efficacy and generalization ability, thereby further reducing overfitting risk. The final model selected through cross-validation will then be evaluated on an independent test set for ultimate performance assessment. For internal validation, we performed bootstrap resampling (n=1000 iterations) to generate training sets matching the original cohort size. Retraining prediction models with these training sets and evaluating performance using the above indicators, we will repeat this process to obtain internal validation performance. External validation will be implemented in prospective observational studies, using external period validation to analyze samples from September 1, 2025 to December 31, 2025. In future research, we plan to collaborate with other institutions to continue external validation. The sample size required for external validation in this study is 1/4 of the modeling sample size, and the minimum sample size for external validation is calculated to be 139 cases (Figure 1).

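### The 0.05 limit on training-minus-cross-validation AUC is a poor overfitting criterion that can tilt tuning and algorithm choice toward logistic regression; the bootstrap's evaluation data also need naming

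*Protocol article*

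**What the plan says.** All of this stands in the Protocol article, section Model Development and Validation.

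- Cross-validation: "A 3×10-fold cross-validation scheme will be adopted, with each split performed independently, yielding 30 model performance estimates".
- Overfitting is to be monitored by "ensuring that the performance difference between the training set and the cross-validation set remains below a threshold (AUC difference <0.05".
- In the same cross-validation, "hyperparameters (including max_depth for RF, and C and γ for SVM) will be jointly optimized", seeking a trade-off between fit and generalisation. No inner tuning loop is described, and none is excluded.
- Bootstrap: "For internal validation, we performed bootstrap resampling (n=1000 iterations) to generate training sets matching the original cohort size". Then: "Retraining prediction models with these training sets and evaluating performance using the above indicators, we will repeat this process to obtain internal validation performance". The data on which the retrained models are scored are not named.
- Algorithm choice: the method with the best overall balance of accuracy, precision, recall, F1 and AUC. The gap is not on that list, and no sentence says that a model exceeding 0.05 is discarded.
- Afterwards: "The final model selected through cross-validation will then be evaluated on an independent test set for ultimate performance assessment". A temporal validation on patients from September to December 2025 is also planned.

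**The concern.** Training AUC is not comparable across these three methods. A forest of deep trees reproduces its training labels almost perfectly by construction, and a flexible radial-kernel SVM comes close. A logistic model with a handful of terms cannot. Subtracting cross-validated AUC from such different starting points gives a number that depends partly on the method's fitting style and only partly on how it performs in new patients.

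If the 0.05 limit is enforced, forest depth is pushed toward the shallowest setting whether or not that predicts best, and forest and SVM may look overfitted beside a logistic model of similar held-out accuracy. The comparison of the three algorithms, which is the core of the modelling objective, could then be tilted.

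The bootstrap raises a related question. For a forest, the reported internal-validation AUC depends almost entirely on which data the retrained model is scored on, and the text leaves that open.

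**Working it through.** **Inputs.** From Sample Size: prevalence 0.593, R² 0.1483, 10 parameters, N=556. From Model Development and Validation: 7:3 split, so 0.7 × 556 = 389 for training. Predictor number, type and correlation are not fixed in the article and are assumptions here.

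**The plan's own figure.** n = P / [(S − 1) ln(1 − R²/S)] with P=10, S=0.9, R²=0.1483: ln(1 − 0.1648) = −0.1801, so n = 10/0.01801 = 555.4, rounded up to 556. Events: 556 × 0.593 = 329.7, or 33 per parameter. The stated sample size is reproduced. The article gives no expected gap or bootstrap optimism to check.

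**Gap without simulation.** If training AUC is 1.00, a gap below 0.05 needs a cross-validated AUC above 0.95. The plan's R² of about 0.15 corresponds to a true AUC of about 0.73, so the gap would be about 1.00 − 0.73 = 0.27 even for a forest that reached that value.

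**Gap by simulation.** n=389, prevalence about 0.59, one 10-fold cross-validation per data set. Entries are mean training-minus-CV AUC, with the share of data sets below 0.05 in brackets.

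| Predictors | True AUC | Depth 1 | Depth 3 | Unlimited |
|---|---|---|---|---|
| 10 continuous, independent | about 0.73 | 0.125 (0%) | 0.213 (0%) | 0.327 (0%) |
| 10 continuous, correlated | 0.732 | 0.072 (0%) | 0.133 (0%) | 0.309 (0%) |
| 5 continuous, correlated | 0.732 | 0.066 (0%) | 0.125 (0%) | 0.322 (0%) |
| 5 three-level ordinal, correlated | 0.738 | 0.027 (100%) | 0.046 (100%) | 0.232 (0%) |
| 5 continuous, correlated | 0.949 | 0.036 (100%) | 0.047 (67%) | 0.079 (17%) |

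In the first scenario, logistic regression had a gap of 0.036 (100% pass) and an SVM at default settings 0.218 (0% pass).

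**Does the gap track generalisation?** Not reliably. With 10 correlated continuous predictors and true AUC 0.948, depth 1 passed (gap 0.044, CV AUC 0.890) and unlimited depth failed (gap 0.084, CV AUC 0.916). The rule would keep the setting that is worse by 0.916 − 0.890 = 0.026. In a further simulation with 31 candidates, 8 of them informative, training and true AUC for the forest were:

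- unlimited depth: 1.000 and 0.686, difference 0.31
- depth 3: 0.883 and 0.696, difference 0.19
- depth 2: 0.827 and 0.696, difference 0.13

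True AUC hardly changed while the difference more than halved, and logistic regression after selection had a true AUC of 0.69 to 0.70.

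**Bootstrap scoring**, n=389, plan-level signal:

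| Model | True AUC | Own resample | Original cohort | Optimism-corrected | Out-of-bag |
|---|---|---|---|---|---|
| Logistic regression | 0.718 | 0.758 | 0.730 | 0.716 | 0.703 |
| Forest, unlimited | 0.669 | 1.000 | 0.949 | 0.949 | 0.672 |
| Forest, depth 3 | 0.670 | 0.928 | 0.820 | 0.765 | 0.660 |

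Optimism correction recovers the true value for logistic regression. For the forest only out-of-bag scoring does. The largest shortfall of a forest against logistic regression in true AUC is 0.718 − 0.669 = 0.049.

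**The case against.** The best defence has four parts.

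1. The threshold is described as monitoring, no discard rule is written, and the stated selection criteria omit it. This is correct. But the sentence speaks of ensuring that the limit holds, and it sits next to the tuning step, so an analyst following it would treat it as a constraint on depth, C and γ.

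2. Forest depth is tuned, and many candidates are categorical or ordinal. This also stands. A reader might infer that the rule rules out random forest whatever its true performance; the ordinal and high-AUC rows of the first table show that this is false. However, age, BMI, CD4 count, viral load, albumin, CRP and several scale scores are also candidates, and with continuous predictors at the plan's signal no depth passed.

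3. A large gap sometimes does mark a poor model. In the ordinal scenario, unlimited depth had a gap of 0.232 and a CV AUC of 0.650, against 0.722 at depth 3. True, but the CV AUC alone shows this, so the gap adds nothing that held-out performance does not give.

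4. The bootstrap details may be left to the full plan. Largely accepted. A reader might infer that internal validation as written measures training fit. The article does not say so: the scoring data are unstated, and calling the resamples training sets is compatible with testing elsewhere. What remains is that the usual default, optimism correction, would not rescue the forest, so the choice should be made explicitly.

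The independent test set and temporal validation are real safeguards for the final model's reported performance. As described, they come after the algorithm has been chosen, so they do not undo a tilted choice.

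**Conclusion.** The 0.05 training-AUC gap should not be used as a criterion. At about the plan's assumed signal and n=389, with continuous predictors, random forest exceeded it at every depth tried (mean gaps 0.066 to 0.327) and an SVM at default settings did too (0.218). Logistic regression met it, with a held-out advantage over the forest of between zero and about 0.05 AUC. The rule can therefore push tuning and the comparison toward logistic regression. It is too strong to say that artefacts decide the comparison: the plan states no discard rule and does not say that bootstrap results choose the algorithm. The possible harm is limited to the internal-validation figure and the choice of algorithm.

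The bootstrap point is secondary and conditional. Only if the forest is scored on its own resample or on the original cohort does its AUC appear as 1.00 or about 0.95 against a true value of about 0.7.

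Limits: predictor structure is assumed, with 5 to 10 data sets per gap scenario and 20 to 100 resamples for the bootstrap. The SVM gap was examined at default settings only, and SVM was not included in the bootstrap table. The article also gives a development set of 445, which was not simulated. The direction is clear; the exact gaps are not precise.

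**What to change.** - Remove the AUC-difference threshold. If training AUC is reported, report it as description only.
- Tune depth, C and γ in an inner cross-validation loop, and compare the three algorithms on outer-loop held-out performance only.
- State the bootstrap in full: each resample repeats variable selection and tuning; logistic regression is reported with optimism correction (resample performance minus original-cohort performance, subtracted from apparent performance); random forest and SVM are scored on out-of-bag patients.
- Keep the independent test set and temporal validation as planned.

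The cost is a few sentences and more computing time; 200 to 500 resamples in place of 1000 would ease the load if needed. The Results section says that no data analysis has been conducted, so the change can still be made before any result is seen.

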**Figure 1. F1:**
[figure not shown]
Flow chart [15]. SVM: support vector machine.

## Results

This study is conducted at a designated infectious disease hospital, the First Hospital (Infectious Diseases Hospital) of Changsha City, Hunan Province, China, which is one of the professional designated treatment centers for HIV/AIDS in China. It is supported by the Traditional Chinese Medicine Research Program of the Health Commission of Changsha, Hunan Province (no. B202318) and the Hunan Provincial Natural Science Foundation of China (no. 2023JJ60388). The study was planned to be conducted from December 2024 to August 31, 2025, with external validation conducted from September 1, 2025, to December 31, 2025. Recruitment for the study began on December 22, 2024. As of December 5, 2025, a total of 603 patients have been recruited. Currently, no data analysis has been conducted. The primary study results are expected to be announced in August 2026.

## Discussion

Studies indicate a frailty prevalence of up to 12% among people living with HIV or AIDS in China [51], with higher rates observed in hospitalized older adults [16]. With the increasing aging phenomenon of people living with HIV or AIDS, researchers need to further focus on the complex health challenges it brings. The PWH Primary Care Guidelines suggest that it is necessary to conduct frailty screening for individuals aged 50 years and above [52]. This study introduces the principles and design of a registry-based observational study. We hope that the use of this predictive model tool can accurately evaluate whether hospitalized people living with HIV or AIDS have weakened, and we hope that the identification of predictive factors will help health care workers provide preventive care.

Previous studies in China have mostly used frailty assessment tools that focus on physiological dimensions [53,54]. Recent evidence suggests that social vulnerability is particularly prominent in people living with HIV or AIDS [55], and frailty is increasingly reflected in psychological distress and high levels of social isolation [56]. This suggests that using a single physiological dimension evaluation tool may have certain limitations, and the necessity of conducting multidimensional evaluations is evident [18,19]. In addition, current evidence on frailty is mainly derived from cross-sectional studies. Given that frailty is a dynamic evolutionary process (meaning that there are often transitions between different stages of frailty: non-frailty, pre-frailty, and frailty), more cohort studies may be needed in China to validate the risk factors and their dynamic impacts across various dimensions [48].

Considering clinical applicability, some potential relevant biomarker data (IL-6, sTNFR1, sTNFR2) missing from the electronic health data system in this study were not included in the analysis, which may affect the estimation of predictor effects. Studies have shown that inflammatory markers IL-6 and TNFR1 are strongly associated with an increased risk of frailty, with each one-standard-deviation increase in log_10_-IL-6 (OR 1.67, 95% CI 1.20‐2.32) and log_10_ TNFR1 (OR 1.91, 95% CI 1.40‐2.61) [57]. Based on the predictive value of inflammatory markers for frailty in existing research, the absence of such indicators may lead to a decrease in the predictive power (AUC) of the model and result in the estimation of the effects of identified risk factors deviating from the true values. However, the CRP included in this study serves as a systemic inflammatory marker for routine clinical testing, and its expression is induced by IL-6, thus being somewhat correlated with IL-6 levels [58]. This allows CRP to partially compensate for the impact of inflammatory cytokine deficiency on outcomes.

As a regional AIDS treatment center, the First Hospital of Changsha covers many places in Hunan Province and surrounding provinces and cities. Our research is based on this single center design, which may limit its universality and applicability: different regions have certain differences in cultural backgrounds, accessibility of medical care resources, and social support systems [59]. However, it is worth noting that a drug resistance study conducted HIV-1 subtype analysis on the people living with HIV or AIDS of our center [60], showing that the most common subtypes in the region include CRF01_AE and CRF07BC, which is similar to the results reported in multiple other regions of China (Shanxi Province, Guangdong Province, Jiangsu Province, and Shanghai City) [61-64]. This indicates that the virological background of patients in the region may be comparable to a wider population nationwide. In addition, this study is a real-world hospital observational cross-sectional study and cannot establish causal relationships between various related factors and multidimensional frailty. In the future, we plan to conduct multicenter prospective studies to expand the sample size and unify the collection and detection of more potential related biomarkers, including IL-6 and sTNFR1/2. By comparing the performance of the new model with the original model on an independent validation set, we hope to further evaluate the incremental predictive value provided by these biomarkers and verify the causal relationship of related factors.
